## Abstract

**Background:**

Type 2 diabetes (T2D) is a leading cause of premature morbidity and mortality globally and affects more than 100 million people in the world’s most populous country, India. Nutrition is a critical and evidence-based component of effective blood glucose control and most dietary advice emphasizes carbohydrate and calorie reduction. Emerging global evidence demonstrates marked interindividual differences in postprandial glucose response (PPGR) although no such data exists in India and previous studies have primarily evaluated PPGR variation in individuals without diabetes.

**Objective:**

This prospective cohort study seeks to characterize the PPGR variability among individuals with diabetes living in India and to identify factors associated with these differences.

**Methods:**

Adults with T2D and a hemoglobin A_1c_ of ≥7 are being enrolled from 14 sites around India. Participants wear a continuous glucose monitor, eat a series of standardized meals, and record all free-living foods, activities, and medication use for a 14-day period. The study’s primary outcome is PPGR, calculated as the incremental area under the curve 2 hours after each logged meal.

**Results:**

Data collection commenced in May 2022, and the results will be ready for publication by September 2025. Results from our study will generate data to facilitate the creation of machine learning models to predict individual PPGR responses and to facilitate the prescription of personalized diets for individuals with T2D.

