### Follow-Up Procedures

Participants are followed for 14 days. They are instructed to wear the CGM and heart rate monitor. The heart rate monitor is to be always worn, including during sleep, and only removed for recharging. Participants are also asked to check their capillary glucose on days 2 through 6 before breakfast and dinner.

Participants log their full dietary intake using the study app or logbook over the 14-day study period, including all standardized test meals and free-living foods (including snacks), beverages (including water), and medications. Participants also log all exercise.

Participants are required to consume protocol-specified meals and to perform light activity, as described in Table 1. The standardized meals consist of vegetarian breakfast foods which participants are to prepare in their homes.

The meals vary in their proportion of carbohydrate, fiber, protein, and fat (refer to Table 2).

**Table 1 table1:** Meal schedule during the at-home study period.

Day and timing			Meal type
**1**			
	Breakfast	Fasting	
	Lunch	As desired	
	Dinner	As desired	
**2**			
	Breakfast	Perceived healthy meal	
	Lunch	Post meal exercise	
	Dinner	Typical mixed protein with dinner	
**3**			
	Breakfast	Fiber supplement with standardized test meal	
	Lunch	Premeal exercise	
	Dinner	Alternative mixed protein with dinner	
**4**			
	Breakfast	Fiber supplement before standardized test meal	
	Lunch	As desired	
	Dinner	As desired	
**5**			
	Breakfast	Protein supplement with standardized test meal	
	Lunch	As desired	
	Dinner	Alternative mixed protein with dinner	
**6**			
	Breakfast	Protein supplement before standardized test meal	
	Lunch	Added fiber with lunch	
	Dinner	Alternative mixed protein with added protein	
**7**			
	Breakfast	Regular breakfast	
	Lunch	Added fruit	
	Dinner	Cooled carbohydrate	
**8**			
	Breakfast	Regular breakfast with added protein	
	Lunch	Added fruit with protein	
	Dinner	Regular carbohydrate	
**9**			
	Breakfast	Protein followed by carbohydrate	
	Lunch	Water 30 minutes before lunch	
	Dinner	As desired	
**10**			
	Breakfast	Standardized test meal	
	Lunch	As desired including dessert	
	Dinner	Protein followed by carbohydrates and vegetables	
**11**			
	Breakfast	Standardized test meal with postmeal exercise	
	Lunch	As desired including desert and cinnamon	
	Dinner	Vegetables followed by protein then carbohydrates	
**12**			
	Breakfast	Standardized test meal with postmeal exercise	
	Lunch	As desired	

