### Statistical Analysis Plan

The study’s primary outcome is PPGR. Following the Wolever and Jenkins method [31], as adapted by Zeevi et al [18], Mendes-Soares et al [20], and Berry et al [32], logged meal times and continuous glucose measurements will be used to calculate the incremental area under the curve. Before conducting analyses, meals logged less than 30 minutes apart will be merged and meals logged within 90 minutes of other meals will be removed. Meals that are very small (<15 g and <70 calories), very large (>1 kg), with implausibly low PPGR values (ie, a PPGR < 5 mg/dL·h after consuming ≥ 40 g of carbohydrates), that are incompletely logged, and which are consumed in the first and last 12 hours of the CGM connection will also be removed. To reduce noise, the median of all glucose values from the 30-minute period before the meal will be taken as the initial glucose level, above which the incremental area will be calculated. Meals that had incomplete glucose measurements in the time window of 30 minutes before and 2 hours after the logged mealtime will be filtered out.

Descriptive statistics will be used to plot the range of PPGRs responses to standardized test meals as well as the correlation between PPGR and the nutritional composition of the logged meals (ie, carbohydrates, fat, and protein).

A machine learning predictor will be developed based on stochastic gradient boosting regression (XGBoost, version 2.2.1; The XG Boost Contributors) [33] using the XGBRegressor class. PPGR will be predicted as the sum of predictions from thousands of decision trees. Trees will be inferred sequentially, with each trained on the residual of all previous trees. The features incorporated in each tree are selected by an inference procedure from features representing meal content (ie, calorie, protein, carbohydrate, and fiber content), meal timing, baseline demographics (ie, age, sex, predominant diet, health conditions, family history, and current medications), baseline survey results (ie, WHO STEPS, WHO-5, Diabetes Distress School, Wilson Adherence Scale, and Pittsburgh Sleep Quality), baseline biometric values (ie, blood pressure, heart rate, weight, height, and body measurements at the upper arm, thigh, calf, waist, and hips), baseline laboratory values (complete blood count, HbA_1c_, blood electrolytes, creatinine, cholesterol, and urinalysis), as well as CGM, heart rate, and activity data.

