Performance will be assessed by holding out 30% of the sample and using 5-fold cross-validation in which cross-validation participants are divided into 5 groups, the model will be trained on the other 4 parts. Random datasets of the same size as the original will be sampled with replacement from the original dataset, and the entire training and validation process will be repeated. The performance will be measured by the ability to accurately predict meals reported by the held-out participants. Prediction results will be aggregated, and Pearson product moment correlation with the measured PPGRs will be reported. The SE for the calculated performance will be assessed using at least a thousand iterations of bootstrapping until the errors stabilize. Model discrimination will be assessed using a binary cut-point for PPGR, set at the 50th percentile of all observed PPGR values, plotting a receiver operating characteristic curve (ROC) and then calculating the area under the ROC.

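### The range plot and the pooled accuracy measures cannot show that people differ in which meals suit them, which the personalized-diet claim needs

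*Protocol article*

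**What the plan says.** The Objective in the Abstract is to "characterize the PPGR variability among individuals with diabetes living in India and to identify factors associated with these differences". The Abstract and the Results section then say that the data will help build prediction models and help "to facilitate the prescription of personalized diets for individuals with T2D". Study Implications (Discussion) and the Conclusion repeat this, pairing variability between people with accurate individual prediction.

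The Statistical Analysis Plan section states these analyses:

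- For the test meals, descriptive statistics to "plot the range of PPGRs responses to standardized test meals".
- For all logged meals, "the correlation between PPGR and the nutritional composition of the logged meals".
- For prediction, "A machine learning predictor will be developed based on stochastic gradient boosting regression", with meal, person, laboratory, monitor and activity features.
- For model performance, "Prediction results will be aggregated, and Pearson product moment correlation with the measured PPGRs will be reported", plus an area under the ROC curve with PPGR split at the median of all observed values.

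Table 1 (Follow-Up Procedures) schedules the standardized breakfast on seven days: fiber supplement with or before it (days 3 and 4), protein supplement with or before it (days 5 and 6), plain (day 10), and "Standardized test meal with postmeal exercise" on both day 11 and day 12.

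**The concern.** PPGR can be split into a person level, an average meal effect, a person-by-meal interaction and residual variation. If the interaction is zero, some people run high and others low on every meal, but the ranking of meals is the same for all. One diet ranking then serves everyone. Only the interaction, and in particular changes of ranking between people, gives tailoring an advantage.

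Large person-level differences are to be expected here: the entry criterion is HbA1c of at least 7.0% with no stated upper limit, on one or more oral agents. A wide range on one breakfast and a good pooled correlation could therefore both come from person level alone. Nothing stated in the article would alert a reader to that, and the results could be taken as support for personalized diets when the meal-specific part is nil.

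**Working it through.** The article gives no figure for this question, so there is none to reproduce. From the article: 1000 evaluable participants (1050 × 0.95 = 997.5) and the seven standardized breakfasts of Table 1, which make six conditions with one repeated. All SDs below, in mg/dL·h, are assumptions.

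**1. The range plot.** The SD across people on one meal is √(person² + interaction² + residual²).
- Person 40, residual 30, no interaction: √(1600 + 900) = 50.0.
- Same, interaction SD 20: √(1600 + 400 + 900) = 53.9.

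A second set of SDs holds the spread fixed, near that of the Israeli study cited in the Discussion (bottom decile at most 15, top decile at least 79).
- Person 25, interaction 0, residual 15: √(625 + 225) = 29.2.
- Person 20, interaction 15, residual 15: √(400 + 225 + 225) = 29.2.

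The spread is identical. In simulation (condition means spread over about 35), one meal is truly lowest for 100% of people in the first case. In the second, the shares over the six meals are about 50, 27, 12, 6, 3 and 1%.

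**2. The pooled accuracy measures.** Take no interaction, person 40, residual 30, and six condition means evenly spaced from 0 to 15 (step 3). The variance of the means is 3² × (6² − 1)/12 = 26.25. A predictor equal to true person level plus average meal effect has

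r = √[(1600 + 26.25)/(1600 + 26.25 + 900)] = √(1626.25/2526.25) = 0.80.

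Its simulated ROC area at the overall median is 0.88. With the second set of SDs the figures are 0.88 and 0.93. These are ceilings for an additive predictor, because it is given each person's true level. A real model must infer that level for held-out participants, but HbA1c, medications and monitor data are among its features.

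**3. Can the breakfasts estimate the interaction?** A simple estimator is the person-by-condition residual mean square over six conditions, minus half the variance of the day 11 to day 12 difference. With 1000 people, person SD 40 and equal, independent residuals of SD 30, simulation gives about 0 (SE about 40) for a true zero and about 400 (SE 43 to 48 across runs) for a true variance of 400.

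That separation depends on the residual assumptions. With the **true interaction zero**:
- *Residual SD s on exercise days, 30 otherwise.* Expected value = (5 × 900 + s²)/6 − s² = (5/6)(900 − s²). For s = 25 this is 229; for s = 20 it is 417. Simulation agrees (about 226 to 228, and 419).
- *Residual correlation ρ^gap by day gap.* Expected value = 900 × (ρ − mean of ρ^gap over the 15 pairs of days 3, 4, 5, 6, 10 and 11). For ρ = 0.2: 900 × (0.2 − 0.059) = 127. For 0.3: 900 × (0.3 − 0.095) = 185. For 0.5: 900 × (0.5 − 0.187) = 282.

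So a zero interaction can appear as roughly 125 to 420, the top of which matches a true interaction SD of 20.

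**The case against.** A reader might infer that the article rests personalized diets on the test-meal range alone and that the collected data go unused. The documents do not support that. The sentence on diets also names the machine learning models. Boosted trees can represent person-by-meal interactions, and the test meals are logged and so can enter the model. This part of the objection stands, and the point is limited accordingly. The model does not close the gap, because its stated measures pool over people and meals and reward person level.

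A reader might also infer that the breakfast data would settle the question cleanly. They would not: the residual comes from one exercise condition on adjacent days, with the biases shown in the working.

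Three further objections have force. A non-zero interaction variance can arise when effect sizes differ but everyone shares the same best meal, so the variance alone is not a sufficient criterion. The six conditions are supplement, timing and exercise variants of one type of breakfast, and Table 2 gives its dish only as an example, so they say little about other foods. The wording is aspirational, and the article sets no rule by which a wide range would lead to recommending personalized diets.

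Finally, a full analysis plan may add more. The point here is not a missing detail: the measures the article does fix do not bear on the use it foresees.

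**Conclusion.** The point holds as a mismatch between stated outputs and intended use. Neither the test-meal range nor the pooled Pearson correlation and median-split ROC area separates people who differ only in level from people who differ in which meals suit them. That follows from how the measures are defined. Its illustrated size (r about 0.80 and area about 0.88 with zero interaction; 50.0 against 53.9 for the spread) rests on assumed SDs. The share of people whose best condition differs from the population's best is 0% without interaction. With interaction SD 20 it is 73% when the condition means are evenly spaced over 15 and 44% when they are spread over 60, so no single share should be quoted.

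It would go too far to say that the study cannot support personalized diets or that its conclusion is false. No result exists yet, the model can hold interactions, and the data allow a useful if imperfect check. This is a cheap improvement worth making.

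**What to change.** 1. **Standardized breakfasts.** Fit a mixed model with condition fixed effects, random person and random person-by-condition. Report the interaction variance with its confidence interval next to the person variance. Read it as an upper bound, because positive correlation between adjacent days inflates it. Add sensitivity analyses for residual correlation that falls with day gap and for a different residual variance on exercise meals. The second must be run over assumed ratios, since only the exercise condition is repeated; a larger exercise-day variance would push the estimate down instead of up.
2. **Prediction model.** In held-out participants, report within-person performance (correlation or meal ranking within person) against an additive person-plus-meal benchmark. Within a person the level cancels, so the benchmark reduces to the average meal effect. The gain over it is the evidence for tailoring, and all logged meals can be used.
3. **Wording.** Base any statement favouring personalized diets on these two results, including whether meal rankings differ between people beyond residual noise, and not on the PPGR range or pooled accuracy.

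The cost is a modest amount of extra analysis on data already collected, with no change to recruitment or procedures. The remaining weakness is that the interaction estimate depends on residual assumptions, which the report should state.

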**Conclusions:**

This study will provide the first large scale examination variability in blood glucose responses to food in India and will be among the first to estimate PPGR variability for individuals with T2D in any jurisdiction.

**Trial Registration:**

Clinical Trials Registry-India CTRI/2022/02/040619; https://tinyurl.com/mrywf6bf

**International Registered Report Identifier (IRRID):**

DERR1-10.2196/59308

## Introduction

Type 2 diabetes mellitus (T2D) is the leading cause of chronic kidney disease, end-stage renal disease, blindness, and nontraumatic amputation; it also substantially increases the risk of myocardial infarction, stroke, and heart failure [1]. Its prevalence is particularly high in India, which is now the most populous country in the world. As of 2023, more than 100 million people living in India have diabetes, representing more than 11% of the population and an additional 136 million have prediabetes [2]. These numbers are anticipated to continue to grow rapidly. The lifetime risk of T2D among 20-year-olds who are obese and living in India is estimated to be more than 86% [3]. The rising prevalence of this condition in India is believed to be the result of changing diets, increasingly sedentary occupations, lower levels of physical activity in the context of urbanization, and rapidly increasing rates of obesity [4].

These trends are particularly concerning because of important differences between the presentation and consequences in T2D among individuals of South Asian origin compared with other racial and ethnic groups. These differences, which often referred to as the “Indian Phenotype” or “South Asian Phenotype” [5-7], are characterized by the onset of T2D at a younger age and substantially lower BMI than people of other races and ethnicities [8-10]. Individuals of Indian origin have higher levels of insulin resistance (and for longer periods of time) and premature beta-cell failure [7]. They are more likely to develop the fatal complications of T2D, most notably heart disease [7]. These features are thought to result from a mix of lifestyle, epigenetics, and fetal programming factors [7,11,12].

The fundamental goal of diabetes management is to maintain near-normal glucose levels. A variety of self-management behaviors, in particular adherence to diet and regular exercise, are central to this goal. An extensive body of evidence demonstrates that aiding patients with T2D with self-management behaviors is associated with improvements in a wide range of outcomes including knowledge, self-care behaviors, weight, quality of life, hemoglobin A_1c_ (HbA_1c_), all-cause mortality, and health care costs [13,14].

Guidelines recommend that nutritional guidance be personalized based on nutritional status, lifestyle, and metabolic goals [15]. Despite this, most dietary advice for individuals with T2D remains generic emphasizing reductions in calories and minimization of carbohydrates [16]. However, there are marked interindividual responses in postprandial glucose response (PPGR) [17]. A study conducted in Israel found substantial PPGR variability to standardized meals for individuals without diabetes [18]. Similar data has been generated in the United Kingdom, the United States, and China [19-21].

There have been no studies characterizing food responsiveness among individuals living in India and virtually no published data, from any judication, in the variability in PPGR for individuals with T2D [22]. Given the unique Indian diabetes phenotype and differences between Indian and western diets, in specific much higher rates of carbohydrate consumption overall [23] and the centrality of white rice and refined wheat [24], there are very likely to be differences in blood glucose responses to food and exercise in India than observed elsewhere, just as there have been in Indians’ responses to diabetes medications [25]. Accordingly, the goal of this study is to characterize and identify factors associated the variability in PPGR among individuals with T2D in India.

## Methods

This prospective cohort study seeks to evaluate the relationship between PPGR and self-management activities including diet, exercise, and other daily routines, for individuals with T2D in India (Figure 1).

**Figure 1 figure1:**
[figure not shown]
Overall study design.

### Study Setting

This trial is being conducted at 14 outpatient clinics in geographically distinct regions across India with population sizes ranging from 1.2 to 34 million. Sites were identified and managed by IQVIA, a multinational contract research organization, and were included if they specialized in the care of individuals with diabetes, had an established research infrastructure for the conduct of diabetes-related studies including a site principal investigator who is a diabetologist (with clinical training in endocrinology or internal medicine), a local ethics committee to provide study oversight, and a sufficient volume of potentially eligible patients. Study enrollment began in May 2022.

### Eligible Participants and Enrollment

The study population consists of adults with diabetes and suboptimal disease control, classified as HbA_1c_ ≥7. Complete inclusion and exclusion criteria are summarized in Textbox 1.

Eligibility criteria required for participants to be enrolled in the study.
**Inclusion criteria**
Age ≥ 18 and <75 years.Physician-diagnosed type 2 diabetes treated with ≥1 oral hypoglycemic agentsHemoglobin A_1c_≥ 7.0% recorded within the past 30 days.Mobile phone capable of running protocol-specified apps.Functional English literacy.
**Exclusion criteria**
Unable or unwilling to provide informed consent or comply with the study-specified procedures.Current use of prandial insulin including a continuous insulin infusion pump.Currently pregnant or planning to become pregnant.Estimated life expectancy of ≤12 months.Active cancer.Myocardial infarction or stroke in the last 6 months.Receiving or planned to initiate dialysis for end-stage renal disease.Receiving oral or intravenous steroids.Any contraindication to using a continuous glucose monitor.

Potentially eligible patients are identified from clinic records and are invited to attend an in-person screening visit at which time eligibility is confirmed and written informed consent obtained. Consenting patients are asked to provide sociodemographic and medical information (specifically, age, sex, predominant diet, health conditions, family history, and current medications) and to complete baseline surveys including the World Health Organization’s STEPwise Approach to Non-Communicable Disease Risk Factor Surveillance (STEPS) survey [26], World Health Organization-Five Well-Being Index (WHO-5) [27]. Diabetes Distress Scale [28], Wilson Adherence Scale [29], and the Pittsburgh Sleep Quality Index [30].

Biometric data including blood pressure, heart rate, weight, height, and body measurements at the upper arm, thigh, calf, waist, and hips, are collected by study coordinators at each site. Finally, enrolled participants provide blood samples including a complete blood count, HbA_1c_, blood electrolytes, creatinine, cholesterol, as well as urinalysis.

After completing baseline assessments, participants are fitted with an Abbott Freestyle Libre continuous glucose monitors (CGM) sensor on their upper, nondominant arm and are provided with a Xiaomi Mi Band Smart Wristband (heart rate monitor) and a Roche Accu-Chek glucometer with testing supplies, and dietary supplements to be consumed with their standardized meals (refer to Follow-up Procedures section). Study-specific apps are downloaded on to the participants’ smartphones to allow them to log dietary intake and synchronize their continuous glucose and heart rate monitors. As a back-up, participants are given a paper dietary logbook and a Freestyle Libre CGM reader with which to collect protocol-specified data.

